## Abstract

**Background:**

The role of dietary patterns in the prevention of unipolar depression has been analyzed in several epidemiological studies. The primary aims of this study are to determine the effectiveness of an extra-olive oil-enriched Mediterranean diet in reducing the recurrence of depression and improving the symptoms of this condition.

**Methods:**

Multicenter, two-arm, parallel-group clinical trial. Arm 1, extra-virgin olive oil Mediterranean diet; Arm 2, control group without nutritional intervention. Dieticians are in charge of the nutritional intervention and regular contact with the participants. Contacts are made through our web platform (https://predidep.es/participantes/) or by phone. Recurrence of depression is assessed by psychiatrists and clinical psychologists through clinical evaluations (semi-structured clinical interviews: Spanish SCID-I). Depressive symptoms are assessed with the Beck Depression Inventory. Information on quality of life, level of physical activity, dietary habits, and blood, urine and stool samples are collected after the subject has agreed to participate in the study and once a year.

**Discussion:**

To the best of our knowledge, the PREDI-DEP trial is the first ongoing randomized clinical trial designed to assess the role of the Mediterranean diet in the prevention of recurrent depression. It could be a cost-effective approach to avoid recurrence and improve the quality of life of these patients.

**Trial registration:**

The study has been prospectively registered in the U.S. National Library of Medicine (https://clinicaltrials.gov) with NCT number: NCT03081065.

**Electronic supplementary material:**

The online version of this article (10.1186/s12888-019-2036-4) contains supplementary material, which is available to authorized users.

## Background

Unipolar depression is one of the leading global causes of disability-adjusted life years (DALYs) [1] and, in 2016, one of the leading causes of Years Lived with Disability (YLD) [2].

Prevention of depression recurrence is an essential goal in the management of depressive patients. Pharmacological treatment strategies are common to help prevent the risk of recurrence, as well as other alternatives, e.g., psychological interventions, which have shown promising outcomes [3].

Besides pharmacological and psychotherapeutic approaches, other interventions based on lifestyle changes, e.g., diet, physical activity, or alcohol and drug limitations, can be helpful can be helpful as part of the treatment of these patients. A body of research suggests the beneficial role of these factors in the etiopathogenesis of the condition and their potential utility for its management [4, 5].

Over the last years, several epidemiological studies have analyzed the role of dietary patterns, foods, food groups and nutrients, as factors that can help prevent unipolar depression. A recent systematic review and dose-response meta-analysis of prospective studies shows that higher quality diets associate with lower risks of developing depressive symptoms, although the authors believe that this hypothesis has to be further tested with prospective studies and randomized controlled trials [6]. Being an emerging promising field of research within nutritional epidemiology, to date there is still scarce evidence [7–9]. One of the dietary factors that has been inversely associated with depression is the adherence to the Mediterranean Dietary Pattern (MDP). Several cohort studies report an inverse relationship between following this healthy dietary pattern and the risk of developing depression [10–12]. Furthermore, two clinical trials carried out with depressive patients found significant improvement regarding depressive symptoms in patients assigned to the MDP [13, 14].

To our knowledge there are not clinical trials specifically designed to assess the role of a nutritional intervention based on the Mediterranean diet in the prevention of depression recurrence.

### Objectives

The primary objective of this study, the PREDI-DEP trial, is to investigate the effectiveness of following an extra-virgin olive oil-enriched Mediterranean diet with the risk of depression recurrence and improvement of residual depressive symptoms in participants with previous episodes of mayor depression. The secondary objectives are to analyze the effect of the Mediterranean nutritional intervention in the quality of life, various biochemical parameters and changes on the microbiota of the participants. We also aim to test the relationship between the nutritional intervention with an extra-virgin olive oil Mediterranean diet with the reduction in the risk of medical and psychiatric comorbidities in patients with a previous diagnosis of unipolar depressive disorder.

## Materials and methods

### Design

Multicenter, two-arm, parallel-group clinical trial. One group of patients (arm 1) is assigned to a Mediterranean diet supplemented with extra-virgin olive oil and the second group (control) (arm 2) has no nutritional intervention. The participants are recruited from four centers across Spain: Hospital [name] (Las Palmas de Gran Canaria), Clínica Universidad de Navarra (Pamplona), Hospital Universitario (Vitoria), and Clínica [name] (Madrid). The intervention period lasted two years.

### Participant eligibility

#### Inclusion criteria

The inclusion criteria were established after an exhaustive review of the scientific literature and consensus among all participating psychiatric and clinical psychologists. Study subjects are aged ≥18 years, has had a previous major depressive episode within the last five years and are in a stage of total or partial remission within the last six months, based on DSM-5 criteria. One participant who has undergone a single depression episode is included for every three participants who had undergone two or more episodes.

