### Randomization

Study participants are randomly assigned to one of two groups (Mediterranean diet or control) once their data are included in a centralized computer system by the specialists. Various stratification factors are considered for the randomization, sex, age group (< 65 years or ≥ 65 years) and recruitment center. At baseline, psychiatrists and clinical psychologists are blinded to the allocation of the participants, following the CONSORT guidelines for randomized trials to prevent selection biases.

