### Sample size and data analyses

The original sample size calculation indicated that 250 people per group were required (assuming an attrition of 5%) to provide a statistical power of 80% for detecting a relative risk reduction of 30% in the Mediterranean diet group versus the control group for a two-year follow-up period. The assumed recurrence rate was 50% for the control group and 35% for the group assigned to the Mediterranean diet. The relative risk reduction of 30% was slightly lower than the observed in the SUN cohort study. In this latter study, we found a 40% risk reduction of depression comparing extreme quintiles of adherence to the Mediterranean Diet Score [23] and the observed among diabetic participants of the PREDIMED trial after three years of intervention with the Mediterranean diet supplemented with nuts [24].

A researcher blinded to the conditions of the intervention will carry out the analysis of the data. Intention-to-treat analysis will be done. For each participant we will compute person-years of follow-up from the study inclusion date to the date of recurrence of the depression or study termination, whichever comes first.

Log Rank analysis will be used to assess the effect of the intervention on the risk of depression recurrence. If distribution differences of baseline characteristics are detected, the Cox proportional-hazards regression models will be used to check by recruitment center, age group and sex, and adjusting for possible confounding factors (educational level, marital status, prevalence of diseases, body mass index, tobacco use, leisure-time physical activity, alcohol intake, total energy intake, type, dose and use of antidepressants, psychotherapy, presence, number, and time since last of depressive symptoms/episodes, and family history of mental disorders). Hazard ratios (HR) and 95% confidence intervals (CI) will be calculated considering the control group as reference.

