## Discussion

Recent studies have assessed the role of the Mediterranean diet in patients with depressive disorders. Jacka et al. reported improvements in depressive symptoms in a sample of 56 depressive patients after 12 weeks of a dietary intervention with a Mediterranean diet in comparison to a social intervention [13]. Similarly, Parletta et al. observed reduced depression and higher quality of life among participants with higher MedDiet scorings in a clinical trial of 95 depressive patients based on the intervention with a Mediterranean diet supplemented with fish [14]. However, these small trials did not evaluate the long-term effect on depression of the Mediterranean diet. Moreover, the aim of the trials was to assess the role of the Mediterranean diet in the treatment of depression and not on its prevention.

The MooDFOOD prevention trial examines the feasibility and effectiveness of two different nutritional strategies (multi-nutrient supplementation and food-related behavioral change therapy). However, it does not examine the effect of a Mediterranean diet intervention in preventing depression in subjects with overweight and have elevated depressive symptoms, but with no current -or in the last six months- criteria for an episode of major depressive disorder [32].

Therefore, to the best of our knowledge, the PREDI-DEP clinical trial is the first randomized clinical trial designed to assess the role of a MDP in the prevention of recurrent depression. Preventing recurrence of depression is one of the priorities in the management of patients with depression, particularly when the number of relapses is high. Whereas the risk of recurrence is approximately 40–60% in patients with a unique depression episode, this risk raises to 90% in patients with three or more previous episodes [33, 34]. Our study provides essential evidence regarding the effectiveness and cost-effectiveness of improving the diet based on a Mediterranean eating pattern for preventing the recurrence of depression and improving the quality of life of patients with previous episodes of depression.

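### Number of previous episodes fixes the recruitment mix, but the article lets it into the analysis only if a baseline imbalance is seen

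*Protocol article*

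**What the plan says.** All references are to the Protocol article.

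- **Inclusion criteria** sets the case mix: "One participant who has undergone a single depression episode is included for every three participants who had undergone two or more episodes". That is 25% with one episode and 75% with two or more, for the trial as a whole. To run the quota, a site must know a participant's episode group at enrolment.
- **Randomization** lists the strata: "Various stratification factors are considered for the randomization, sex, age group (< 65 years or ≥ 65 years) and recruitment center". Episode group is not among them, so nothing holds the 1:3 ratio within each arm.
- **Sample size and data analyses** names the primary test: "Log Rank analysis will be used to assess the effect of the intervention on the risk of depression recurrence". No strata are given. Adjustment follows under a condition: "If distribution differences of baseline characteristics are detected, the Cox proportional-hazards regression models will be used to check by recruitment center". The long list of adjustment factors in that sentence includes "psychotherapy, presence, number, and time since last of depressive symptoms/episodes".
- **Discussion** gives recurrence risks by episode history. It states that "the risk of recurrence is approximately 40–60% in patients with a unique depression episode", and puts the risk at 90% after three or more episodes. No time horizon is attached to either figure.

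**The concern.** A variable important enough to fix the composition of the sample, and known for everyone before allocation, would normally be used in the primary analysis as a matter of course. Here its use depends on what the baseline table shows. This has three consequences.

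1. The arms may differ by chance in their share of single-episode participants, and the crude comparison carries that difference.
2. Whether the reported hazard ratio adjusts for episode history is settled after the data are seen.
3. If the arms happen to be balanced, no adjustment is triggered. An unstratified log-rank test that pools groups with different hazards still loses some power, because the pooled hazard ratio lies closer to 1 than the ratio within each group.

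**Working it through.** **Inputs.** From the article: 250 per group, 5% attrition, 80% power, two-year recurrence of 50% (control) and 35% (diet), and a quota of 25% to 75%. Assumed: two-sided 5% significance (the article states no level), exponential event times, and two-year risks by episode group, which the article does not give.

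**The plan's own figure.** Comparing 50% with 35% at 80% power needs 170 per arm, or 170/0.95 ≈ 179 after attrition (183 and 193 with continuity correction). The stated 250 is not reproduced; it exceeds what the stated inputs need. That is a separate matter, but it bears on size here. With 250 × 0.95 = 237.5 evaluable per arm, power is about 91% for two proportions.

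**Planned hazard ratio.** Under exponential times, 50% versus 35% gives HR = ln(0.65)/ln(0.50) = 0.621. An HR of 0.70 would instead give a diet-arm risk of 1 − 0.50^0.70 = 38.4%, a smaller effect than planned.

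**Chance imbalance.** SD of the difference between arms in single-episode share:

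√(2 × 0.25 × 0.75 / 250) = 0.0387, or 3.9 points.

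The 95% range is 1.96 × 3.87 = ±7.6 points. The chance of a gap above 5 points is about 20%, and above 10 points about 1%.

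**Effect on the crude difference.** Shift = gap in share × gap in risk between episode groups:

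- risk gap 13 points: 7.6 × 0.13 ≈ 1.0 point
- risk gap 40 points: 7.6 × 0.40 ≈ 3.0 points

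The planned difference is 50 − 35 = 15 points. The shift is for a gap at the edge of the 95% range; most allocations would give less.

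**Power at the planned effect.** Simulation with 237 per arm, HR 0.621 in both episode groups, episode group not balanced by the allocation, and 6,000 runs per row (Monte Carlo error about 0.4 points). The first three rows keep the pooled control risk at the planned 50%. The last three read the Discussion's risks as two-year risks and give the 90% to everyone with two or more episodes, which is an upper bound.

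| Control risk, one / two or more episodes | Unstratified | Stratified | Gain (points) |
|---|---|---|---|
| 40% / 53% | 91.6% | 92.1% | 0.5 |
| 30% / 57% | 90.8% | 92.2% | 1.4 |
| 20% / 60% | 89.5% | 92.3% | 2.8 |
| 60% / 90% | 98.7% | 99.4% | 0.7 |
| 50% / 90% | 98.1% | 99.6% | 1.5 |
| 40% / 90% | 95.8% | 99.3% | 3.4 |

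With no true effect, both tests rejected in about 5% of runs (4.7% to 5.4%).

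**Power at a smaller effect.** At HR 0.70, unstratified against stratified power is about 70% and 73% for risks of 25%/58%, and 85% and 88% for 50%/80%. For 50%/90%, separate runs gave 85% and 91%, and 84% and 93%, a gain of 6 to 8 points. The extreme pairing of 40%/90% gave 80% and 91%.

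**The case against.** The strongest reply is that nothing here is an error. A quota controls case mix, and no rule makes a quota variable a randomisation stratum. Three strata instead of four is an ordinary trade-off: sex, age group and four centres already make 2 × 2 × 4 = 16 cells, and episode group would make 32. Number of episodes is a named adjustment factor, and chance imbalance is the very case the conditional Cox models address. A condensed article may also leave the stratification of the log-rank test to a fuller document.

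Much of this stands, and it rules out several stronger readings that a reader might infer:

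- *That the comparison is biased or the test invalid.* It is not. Allocation is random and the type I error holds.
- *That the imbalance is accepted for nothing.* The conditional Cox models are a partial remedy.
- *That episode history is the strongest predictor.* The article ranks no predictors; it only gives figures for this one. Its 90% is for three or more episodes, while the quota divides at two or more.
- *That the trial loses substantial power.* Gains of 6 to 8 points or more need both an HR of 0.70 and the Discussion's risks read as two-year risks. With 50%/90% the pooled control risk would be 0.25 × 50 + 0.75 × 90 = 80%, not the planned 50%.

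One point does not fall to the reply. The article does not merely leave adjustment open; it states a trigger for it. That trigger applies to every listed covariate, but it matters most for one that the design itself uses.

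**Conclusion.** The point holds as a modest, cheaply removed weakness. A prognostic variable that fixes the sample's composition is used in the analysis only if the data prompt it. The cost is a data-dependent headline hazard ratio, chance imbalance of up to about 7.6 points in single-episode share (moving the crude difference by about 1 to 3 points against 15), and about 0 to 3.5 points of power at the planned effect. Unstratified power remains near 90% or above, against the 80% sought.

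The imbalance range follows from the article's figures alone. The shift and the power figures rest on assumed two-year risks by episode group, exponential times, a common hazard ratio and a two-sided 5% level. A larger loss, about 8 points, needs HR 0.70 with 50%/90% as two-year risks; only the still more extreme 40%/90% pairing goes beyond that. The documents support neither scenario as the planned one.

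**What to change.** State that the primary log-rank test, and the Cox model that gives the headline hazard ratio, are stratified by episode group (one versus two or more), whatever the baseline comparison shows. Remove the imbalance trigger for this variable. Fix this before outcomes are compared by arm.

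The cost is one or two sentences. The variable is already recorded to run the quota, and at 500 participants the two strata would hold about 125 and 375 people. Stratification did not lower power appreciably in any scenario examined.

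Adding episode group to the central randomisation is optional. It would limit imbalance at source, but 32 cells for 500 participants average about 16 each and some would be sparse. If recruitment is well advanced, leave the allocation as it is; the analysis change alone meets the point.

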#### Exclusion criteria

Table 1 shows the exclusion criteria in the PREDI-DEP trial:

**Table 1 Tab1:** Exclusion criteria in the PREDI-DEP trial

1. Presence of comorbid psychiatric disorders (current mania/hypomania or a history of bipolar disorder, psychosis or schizophrenia, predominant anxiety disorder, primary personality disorder, substance abuse or eating disorder)	
2. Suspicion of depression (Score > 18 in Beck Depression Inventory) [16]	
3. Participants with severe medical conditions with low survival	
4. Participants with history of food allergy with hypersensitivity to any of the components of olive oil or nuts, presence of disorders of chewing or swallowing or a low predicted likelihood of changing dietary habits according to the Prochaska and DiClemente stages of change model [35]	
5. Institutionalized patients and those participants who lack autonomy	

### Patient recruitment

In a first phase of the selection process, we extract names of potential participants from the clinical records of the hospitals or health centers who are willing to collaborate with the study. Next, the participating psychologists and psychiatrists review the clinical records individually to identify the subjects that comply with the inclusion criteria. The potential participants are contacted by phone or during a clinical visit. When a candidate agrees to participate, a face-to-face interview with the specialist is carried out to exclude participants who do not meet the criteria. Besides the semi-structured clinical interview (Spanish SCID-I) [15], participants also self-complete the Beck Depression Inventory to assess depressive symptoms [16]. Information about the participant is completed with questions from the eligibility questionnaire, such as medical conditions or problems related with the adherence to the Mediterranean diet. During the first visit, participants receive a brief explanation of the study, are informed that are going to be given extra-virgin olive oil for the duration of the trial at no cost, and a signed informed consent is obtained. All study participants are asked to provide blood samples (previous appointment with the hospital) and a subgroup of participants is instructed to also provide urine samples (recruitment centers: Vitoria, Pamplona) and stool samples (recruitment center: Vitoria).

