### Intervention with the Mediterranean diet and control group

Full-time registered dietitians with experience in the PREDIMED trial are responsible for the dietary intervention in the PREDI-DEP study. The PREDIMED trial is a landmark trial of intervention with a Mediterranean diet in participants at high risk of cardiovascular disease [17, 18]. The methodology in PREDI-DEP is similar to that in PREDIMED.

Participants allocated to the Mediterranean diet receive intensive training on Mediterranean diet and supplemental foods (Table 2), as well as extra-virgin olive oil (one liter of extra-virgin olive oil rich in polyphenols every two weeks), at no cost. The authors have no conflict of interest with any food company.

**Table 2 Tab2:** Intervention with Mediterranean diet

Intervention	Periodicity	Instrument
Free food supply	Quarterly	Collected by participants in medical centers
Book and information regarding Mediterranean Diet	Initial	Collected by participants in medical centers
Buying foods list, plan of meals, cooking recipes, menus	Quarterly	Collected by participants in medical centers
Compliance degree, personalized goal achivement	Quarterly	Telephone
Mediterranean Diet news	Monthly	Web/e-mail
Clarification of doubts, suggestions	Any moment	Any instrument

At the beginning of the trial, the dieticians thoroughly explain the reasons to follow a Mediterranean diet to each participant and negotiate changes in his/her diet, working with the subject to determine what he or she considers an attainable goal. The dietician does this every three months by calling the participant over the phone. To assess adherence to the Mediterranean diet and enhance future adherence (Additional file 1), the dietitians use a validated 14-point Mediterranean Diet Assessment Screener (MEDAS) [19], which was employed in the PREDIMED trial.

Every three months the participants receive written material with information on key Mediterranean foods and seasonal shopping lists, menus and specific recipes for a typical week. This material is discussed in detail with the dietitians.

The website developed for this study (https://predidep.es/participantes/) is updated monthly with news related to the Mediterranean diet and its health effects. The dieticians take into account any doubt or suggestion made by the participants at any time of the intervention period.

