No nutritional intervention is employed with the control group. These participants have an email and access to the website of the project, but with limitations on the contents related with the intervention. To prevent these subjects from withdrawing from a study an incentive at trial termination is offered.

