### Assessment of exposure

#### Baseline information

The dieticians have the first contact with the participants over the phone to inform them in which arm they have been allocated and give instructions to the subjects who have been assigned to the Mediterranean diet as where and when to collect the food supply. Moreover, the dieticians complete the information for each participant through: 1) a general questionnaire; 2) a physical activity questionnaire; 3) a semi-quantitative food frequency questionnaire (FFQ); 3) the 14-Item Mediterranean Diet Adherence Screener (MEDAS), and 4) the Short Form-36 Quality of Life Questionnaire (SF-36).

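### As the article describes it, every participant is promised free olive oil at the first visit, but only the diet arm receives it

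*Protocol article*

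**What the plan says.** Five places in the protocol article bear on the point.

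- Patient recruitment: at the first visit participants get a brief account of the study, "are informed that are going to be given extra-virgin olive oil for the duration of the trial at no cost", and sign consent. The sentence does not mention allocation.
- Randomization: each person is "randomly assigned to one of two groups (Mediterranean diet or control) once their data are included in a centralized computer system by the specialists". Psychiatrists and clinical psychologists are blinded to allocation at baseline.
- Baseline information: "The dieticians have the first contact with the participants over the phone to inform them in which arm they have been allocated". In that call only those assigned to the diet are told where and when to collect food.
- Intervention with the Mediterranean diet and control group: "Participants allocated to the Mediterranean diet receive intensive training on Mediterranean diet and supplemental foods (Table 2), as well as extra-virgin olive oil", at one litre every two weeks. For the other arm, "No nutritional intervention is employed with the control group"; the Design section says the same.
- The same Intervention section adds, about controls: "To prevent these subjects from withdrawing from a study an incentive at trial termination is offered". The incentive is not described.

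The section on sample size and data analyses plans 250 people per group and a single attrition figure of 5%, not split by arm.

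**The concern.** The first-visit sentence and the description of the arms cannot both hold as written. A participant who agrees partly because of free oil, and is then randomised to control, learns by telephone after consenting that none will come.

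Two consequences are plausible in a trial where participants know their arm. Controls may withdraw more often than diet participants. Controls who stay may also report more symptoms out of disappointment. The second matters for the Beck Depression Inventory, which participants complete themselves. It measures residual depressive symptoms, which are part of the primary objective, and a suspicious score also prompts an extra specialist appointment. Recurrence itself is diagnosed by specialist interview and is less exposed.

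**Working it through.** **Order of events.** The article gives no explicit timeline, but its sections fit only one order:

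1. Interview, explanation and consent at the first visit (Patient recruitment).
2. Data entry by the specialists, then random assignment (Randomization).
3. Telephone call from the dietician disclosing the arm (Baseline information).

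The oil statement belongs to step 1, when no participant has been told an arm. The specialists who hold the interview are blinded at baseline, so the statement cannot readily be read as something said only to people already allocated to the diet.

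**What each arm is given.**

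| | Told at first visit | Given during the trial | Given at the end |
|---|---|---|---|
| Diet arm | Free oil throughout | Free oil, food supply, training | Nothing stated |
| Control arm | Free oil throughout | No dietary programme | Unspecified incentive |

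The control row does not match. Even if the closing incentive were oil, it would come at termination and not throughout the trial.

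**How many are affected.** With 250 per group, the total is 2 × 250 = 500. The statement is untrue for 250/500 = 50%. The group size is used here only as a count. It is not reproduced by the stated inputs: 50% against 35% at 80% power, with two-sided alpha of 0.05 assumed, needs 170 per arm, or 170/0.95 = 179 with 5% attrition. That is a separate matter and does not affect this point.

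**Can the effect be sized?** No loss figures by arm are given, so the following only shows what the answer would depend on. Diet-arm loss is held at 5% (237.5 remaining) and recurrence at 50% against 35%.

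*Power, if loss is unrelated to risk.* For two proportions with pooled null variance:

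z = (0.15 − 1.96·SE₀)/SE₁, where SE₀ = √[p̄(1−p̄)(1/n_c + 1/n_d)] and SE₁ = √[0.25/n_c + 0.2275/n_d].

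- Control loss 5%, n_c = 237.5: SE₀ = 0.0454, SE₁ = 0.0448, z = 1.36, power 91.3%.
- Control loss 15%, n_c = 212.5: SE₀ = 0.0466, SE₁ = 0.0462, z = 1.27, power 89.8%.
- Control loss 25%, n_c = 187.5: SE₀ = 0.0482, SE₁ = 0.0479, z = 1.16, power 87.7%.

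All three exceed the planned 80%.

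*Bias, if leavers differ in risk and their recurrences are never found.* With control loss d and risk r among leavers, observed control risk = (0.50 − d·r)/(1 − d).

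- d = 0.15, r = 0.50: 0.425/0.85 = 0.50; risk ratio 0.35/0.50 = 0.70, unchanged.
- d = 0.15, r = 0.70: 0.395/0.85 = 0.465; risk ratio 0.35/0.465 = 0.753.
- d = 0.25, r = 0.70: 0.325/0.75 = 0.433; risk ratio 0.35/0.433 = 0.808.

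Leavers at lower risk than the rest would move the ratio the other way. Since d, r and the share of recurrences missed are all unknown, neither the size nor the direction follows from the document.

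**The case against.** The strongest reply is that this is one loosely worded sentence in a condensed article. Its grammar is broken, and a conditional may have dropped out. The brief account of the study that precedes it may well have covered random allocation and the control arm. This stands as a limit: a reader might infer that the consent form was wrong, and the article does not show that, because the form is not available. It does not remove the contradiction between the sections.

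Three further inferences are tempting, and the document does not support them.

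- *Controls might receive oil, so the comparison is contaminated.* The Design, Intervention and Baseline information sections all confine the dietary supply to the diet arm. Controls might adopt the diet on their own, but no rate is given. Assuming that 20% do so with full effect, control risk would be 0.8 × 0.50 + 0.2 × 0.35 = 0.47 and the risk ratio 0.35/0.47 = 0.745. Both inputs are invented, and full effect without training or oil is an extreme case.
- *The hazard ratio and power shift by a known amount.* Assumed control loss of 15–20% against 5% can be made to move the hazard ratio from 0.62 to 0.66–0.68 and power from 93% to 78–84%. That happens only if people lost are counted at risk to study end and their later recurrences stay unseen. It is a question about the follow-up rule, not about the oil statement. Under ordinary censoring unrelated to risk the hazard ratio stays near 0.62. The section on recurrence of depression also says that specialists search the clinical records of those lost, which recovers some events.
- *The sentence causes withdrawal.* Controls in any unblinded diet trial may leave once they know their arm. The article anticipates this and offers an incentive, but nothing in it ties withdrawal to the oil statement.

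**Conclusion.** The contradiction holds. As the article describes the procedure, free oil throughout the trial is promised to all before the arm is known and supplied to one arm only, so the statement is untrue for about half of the 500 planned participants. This assumes the equal groups implied by 250 per group and the order of events that the sections imply.

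The consequences are possible but unmeasured: some added control withdrawal, and some disappointed self-report on the Beck Depression Inventory. The record review and the closing incentive lessen the first but do not correct the information given. It should be corrected as a fault in the described recruitment information. It is not a demonstrated fault in the consent form, and it is not evidence of a quantified bias or loss of power.

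**What to change.** Reconcile the Patient recruitment section with the Intervention section. The first-visit explanation should state that:

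- allocation is by chance;
- oil during the trial goes only to those allocated to the diet;
- those allocated to control have no dietary programme and receive the incentive at the end, with the incentive named.

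Check the consent text and amend it in the same way if it carries the same sentence. The cost is a minor amendment to the script or consent form, and possibly slightly slower recruitment once candidates know that the oil depends on allocation. The analysis and the sample size need no change on this account.
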